## Abstract

**Introduction:**

Excessive daytime sleepiness (EDS) is a key symptom for patients with obstructive sleep apnea (OSA). Despite important limitations in the longitudinal monitoring of EDS, the Epworth Sleepiness Scale (ESS), the Maintenance of Wakefulness Test, and the Multiple Sleep Latency Test (MSLT) are the best available objective tests to predict EDS. Limited information exists on the day-to-day fluctuations of sleepiness symptoms from the everyday life perspective of OSA patients. The most feared is sudden sleep episodes that cause traffic accidents. The following study protocol investigates the novel possibilities of ultra-long-term Electroencephalography (EEG) (ULT-EEG) home monitoring in sleepy OSA patients with a subcutaneous implant. We hypothesize that the high-frequency testing from ULT-EEG, in combination with an ecological momentary assessment (EMA), can provide the information to develop new electrophysiological monitoring of sleep propensity as an alternative to the well-established, yet subjective, ESS.

**Methods:**

This clinical exploratory and experimental study will include 15 treatment-naïve patients with severe OSA, with a baseline ESS score above 10. The subjects will be implanted with a two-channel subcutaneous EEG monitoring device upon inclusion and a confirmative polysomnography MSLT. Subcutaneous EEG is recorded 24/7 for 6 weeks before and 6 weeks during continuous positive airway pressure (CPAP) treatment. Daily assessments with the Karolinska Sleepiness Scale, the Psychomotor Vigilance Task test, and a sleep/nap diary will be collected using EMA methods.

**Discussion:**

This study combines data collection from sleepy OSA patients' natural environments using ULT-EEG and EMA methods to obtain sleepiness metrics suitable for developing and preliminarily validating the possibilities of ULT-EEG sleepiness monitoring. We aim to prove a new concept of monitoring sleepiness symptoms in OSA patients and gain new insights into CPAP-related sleepiness rehabilitation.

**Ethics and dissemination:**

All participants will provide written informed consent to participate in this study. Ethical approval from the Region Zealand Ethics Committee on 13/09/2021 (SJ939, EMN-2021-06803). The study will be conducted in accordance with local legislation and institutional requirements and comply with the Declaration of Helsinki and the General Data Protection Regulation (GDPR).

## 1 Introduction

### 1.1 Background

Sleeping at the wheel is a feared complication for obstructive sleep apnea (OSA) patients living with excessive daytime sleepiness (EDS) (Higgins et al., 2017). Additionally, severely decreased quality of life and increased comorbidity and mortality are linked to EDS (Gooneratne et al., 2011). The Epworth Sleepiness Scale (ESS) is often used to clinically assess sleepiness in OSA patients, and it aims to determine average sleep propensity (Johns, 1991). The ESS constructs a standardized hypothetical test setting by asking the subject to estimate their risk of dozing off or falling asleep recently in eight everyday situations with different soporific characteristics. Yet, often, raters have not encountered these situations recently. Recall bias can either under- or overestimate the results, and the patient/doctor relationship plays an important role because the doctor gatekeeps specific solutions or restrictions that interfere with scoring the ESS, for example, the access to wake promoters in patients with residual EDS or situations in which driver-license suspension is at stake, to name some. Regarding the latter, L. Grote et al. have very clearly shown a double ESS score reduction for OSA patients starting CPAP treatment who were involved a driver's license certification process because of ongoing EDS even though the baseline ESS scores did not differ (Grote et al., 2018).

Objectively testing EDS in OSA patients is possible using the Multiple Sleep Latency Test (MSLT) and the Maintenance of Wakefulness Test (MWT). Determining the average sleep propensity using the MSLT, the MWT, or the ESS utilizes specific standardized conditions to determine the likelihood of falling asleep. This creates high reliability, but it poorly depicts the everyday context of sleepiness symptoms that often are far from these test conditions. These objective tests say much about how a subject performs in a specific test setting on a particular day, but translating that into an everyday setting is often a clinical challenge (Grote et al., 2018). Furthermore, the laboratory setting bypasses the patients' coping strategies for handling the EDS. The MSLT and the MWT are resource-intensive, and their utility as EDS-monitoring possibilities for the global OSA population, which is approaching 1 billion people (Pizza et al., 2013), is impossible.

In sleep medicine, the ability to use 24-h polysomnography (PSG) to predict MSLT results in the diagnostic workup of central hypersomnia has been shown (Pizza et al., 2013). A few attempts at recording Electroencephalography (EEG) as a measure of sleepiness in a subject's everyday life can be found in the scientific literature (Möller et al., 2009).

As sleep pressure regulation is a longitudinal phenomenon controlled by homeostatic and circadian processes, this phenomenon must be continuously monitored to optimally assess hour-to-hour, day-to-day, and week-to-week changes.

Microsleep (MS) episodes (Skorucak et al., 2020a; Moller et al., 2006) and frequency changes with increased theta power and decreased alpha power (Strijkstra et al., 2003) are some of the EEG-derived sleepiness markers suitable for a more hour-to-hour or day-to-day monitoring ability and have been found to correlate to performance measures (Moller et al., 2006).

In recent decades, technological advancements have brought forth devices capable of continuous EEG monitoring for weeks and up to years (Möller et al., 2009). One such device, the 24/7 EEG™ SubQ, can obtain good-quality and clinically relevant EEG data in this ultra-long-term perspective (Weisdorf et al., 2019). This offers a previously inaccessible great longitudinal dispersion but limited spatial resolution compared to standard EEG or the PSG mock-up, which has traditionally been limited to day(s)-long data recording. Recent studies found that despite the limited spatial resolution of ULT-EEG, automated EEG analysis for sleep–wake characterization performs well (Gangstad et al., 2019; Weisdorf et al., 2018).

The American Academy of Sleep Medicine (AASM) defines EDS as “the inability to maintain wakefulness and alertness during the major waking episodes of the day, with sleep occurring unintentionally or at inappropriate times almost daily for at least 3 months” (Lukacs and Bhadra, 2014). Likewise, the ESS asks the subject to estimate the risk of dozing off in “recent times”. With ULT-EEG recording systems, obtaining consecutive EEG throughout “recent times” is now possible. According to EDS definitions, sleep occurs as episodic intrusions during daytime wakefulness. This phenomenon is potentially measurable and, therefore, quantifiable. We hypothesize that this possibility will enable us to objectively measure what the ESS asks the patient to estimate.

### 1.2 Rationale for conducting this study

To the best of our knowledge, no previous study has been conducted recording ULT-EEG from OSA patients suffering from EDS to detect the degree and distribution (weekly/daily) of sleep phenomena in the patient's everyday life and during normal wake hours. In addition, limited knowledge is found on the effects of CPAP treatment on the rehabilitation from EDS from the perspective of day-to-day and week-to-week variations and CPAP therapy time.

There are many implications for the documentation and quantification of such sleep phenomena:

A biomarker of OSA disease severity and CPAP treatment efficacy, as well as any other treatment attempts to reduce EDS.A clinical tool in the evaluation of fitness to drive and safety assessments regarding the sleepy OSA patient.Select OSA patients suffering from CPAP treatment-resistant residual sleepiness to guide indication of add-on wake promoters (e.g., solriamfetol).

### 1.3 Hypotheses

We hypothesize that at-home ULT-EEG monitoring can be used to monitor brain activity to the extent that quantification of sleep intrusions in the daytime can be detected in the natural environment of patients suffering from EDS due to OSA.

This suggests a potential new methodology for quantifying physiological sleep pressure or average sleep propensity derived directly from the patient's natural environment, taking into consideration patient-specific coping and other behaviors.

We believe that ULT-EEG measured at home holds novel information to bring forth biomarkers suitable for OSA patients and aid in better treatment-effectiveness monitoring and safety assessments. This study will serve as a proof of concept for using ULT-EEG monitoring when evaluating EDS in OSA patients.

### 1.4 Objectives

This project aims to develop new sleepiness biomarkers using ultra-long-term at-home EEG monitoring as a novel, new data type. We will conduct a clinical study exploring electrophysiological sleep/wake transition phenomena in a population with OSA and EDS by making ultra-long-term subcutaneous EEG recordings in subjects' real-life conditions before treatment and as they start treatment.

We follow an explorative objective and an experimental one. We aim to validate our explorative findings in an experimental setting.

Our *explorative* objective is to scrutinize subcutaneous ULT-EEG for potential biomarkers predicting sleepiness in OSA patients. Determining daytime wake-to-sleep transition rate, microsleep episodes, and macro-sleep episodes, alongside the duration and patterns of these events. In addition, vigilance determination of the odds ratio product (ORP) (Younes, 2023) or Vigilance Algorithm Leipzig (VIGALL) (Olbrich et al., 2015) can be assessed. Our explorative findings will be correlated and preliminarily validated against the well-established sleepiness metrics and questionnaires, the MSLT, the ESS, the Karolinska Sleepiness Scale (KSS), and the Psychomotor Vigilance Task (PVT) test, as well as patients' experiences of falling asleep or dozing off in the form of a “sleep and nap diary”. Any potential sleepiness biomarker derived from this study will be available for future confirmatory trials.

Our *experimental* objective is to determine the effects of CPAP treatment on sleep quality, quantity, and timing from the day-to-day perspective that ULT-EEG provides. Furthermore, the experimental design enables us to clinically validate the exploratively deduced sleepiness biomarker candidates through comparisons before and after the intervention of CPAP treatment conditions. Previous studies on CPAP's effect on reducing sleepiness have shown a dose-dependent configuration with CPAP usage. ESS scores are typically reduced by 4.75 points (Patel et al., 2003). We expect relevant biomarker candidates to follow similar patterns when CPAP is introduced in a population with severe OSA and EDS.

Our *secondary objective* is to validate automatic sleep/wake classification based on two-channel subcutaneous EEG against golden standard manually scored polysomnography in patients with severe OSA. Additionally, we explore using ecological momentary assessment (EMA) methods to record excessive daytime sleepiness in patients with OSA and collect passive sensor data from participants' smartphones to assess physical activity.

### 1.5 Study design

This study is a clinical prospective exploratory and experimental study of patients suffering from EDS because of severe OSA.

We include 15 treatment naïve severe sleep apnea patients with an ESS score above 10. See Figure 1 for an overview of the study flow. The subjects enter the study as new referrals to the sleep clinic at Zealand University Hospital, Denmark, and will, after inclusion, start the study with a pretest with a PSG, followed by an MSLT. If these test results conflict with the inclusion and exclusion criteria the subject will be excluded from the further study.

**Figure 1 F1:**
[figure not shown]
Patients screened according to predefined inclusion/exclusion criteria and found eligible and willing to participate will follow a timeline of PSG and MSLT. Implantation of 24/7 SubQ EEG device. Six weeks recording of subcutaneous EEG, daily sleep diary and episodes of daytime sleeping, weekly ESS scores, and daily KSS scores and PVT scores. Start CPAP treatment. Six weeks of recording with a collection of CPAP usage data. Explanation of 24/7 SubQ EEG device. End of study. AHI, Apnea-Hypopnea Index; ESS, Epworth sleepiness Scale; PSG, polysomnography; MSLT, Multiple Sleep Latency Test; PVT, Psychomotor Vigilance Task test; KSS, Karolinska Sleepiness Scale; CPAP, continuous positive airway pressure.

The subjects will have the UNEEG™ SubQ implanted (24-7 EEG™ SubQ”), and after approximately 10 days of healing, they will start wearing the external recorder as much as possible for the following 12 weeks. CPAP treatment is started 6 weeks after the start of ULT-EEG recording. Two secondary PSGs will be performed after implantation: the first prior to OSA treatment initiation and the second after. During the ULT-EEG recording, simultaneous recording of weekly ESS scores and a daily sleep diary will be performed through the participants' smartphones. Additionally, 14 days before and during CPAP treatment, the KSS and PVT test will be performed four times daily. For further information on these assessments, see Section 2.4 “Study Procedures.”

### 1.6 Study endpoints

• ULT-EEG is analyzed to assess potential electrophysiological biomarkers resembling sleepiness or sleep pressure, such as wake–sleep transition rate, timing, and daytime sleep patterns in the micro and macro perspective or vigilance state classification. This will be assessed through automated microsleep detection and automated sleep-stage classification methods. Using concomitant PSG and ULT-EEG, we will identify the markers of stage transition from awake to dozing/light sleep in the SubQ recording. We will do this both according to AASM criteria and in shorter segments of EEG. From this template, we will use machine learning (ML) techniques to train a classifier to detect those short transitions in the ULT-EEG recording with different levels of sensitivity and specificity.

• The correlation between ULT-EEG-derived biomarker candidates and well-known sleepiness metrics, such as the mean sleep latency and EMA collected reaction time, and ESS and KSS scores, as well as patient reports of episodes of daytime sleeping or dozing off (nap diary). From the timestamps on PVT prompts to patients, we will identify segments of interest in the ULT-EEG recording to document changes in EEG-related signs of reduced vigilance. We will use this to validate the responses on the clinical scales given by patients.

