#### 2.4.4 EMA and mobile sensing

EMA is a method for assessing patient-reported outcome measures (PROMs) in the actual situation being assessed. PROMs are always reported in a context in which the reporting might interact. In EMA studies, subjects can be tested in the context they are actually in, such as at home. EMAs are typically collected using a smartphone app installed on participants' phones. This approach has great advantages over paper and pencil, including reducing errors, avoiding “backfilling” of the sleep diary, and providing digital timestamps with exact time registrations for when the subject completed their PVT test and KSS. Furthermore, participants have been shown to have their smartphones with them at all times, including nighttime, which makes it a well-suited platform for home-based sleep studies.

This study collects subjective sleepiness scores, PVT test scores, and sleep diary data by prompting subjects to register these on their smartphones. The active collection of EMA data is supplemented with simultaneous passive mobile sensing, collecting GPS-determined location, step counts, activities detected by the phone (e.g., walking, running, and biking), screen events, battery time, and local weather data. This set of passive sensing data helps build a rich contextual picture of participants' activity levels and temperature exposure during the study. These factors are all relevant to sleepiness perception in the everyday setting. In determining sleepiness levels, it is evident that it is a situational phenomenon, and clinical variability, for instance, ESS scores, has been reported with significant day-to-day or within-day variance that was probably explained by situational sleepiness (Grewe et al., 2020).

In this study, we use the Copenhagen Research Platform (CARP) and the CARP Mobile Sensing Framework (Bardram, 2022, 2020) to collect the active EMA PROMs and the passive sensing data. CARP is an open-source research tool designed for digital phenotyping, accessible on both Android and iPhone (iOS) smartphones. In this study, data will be collected by the Technical University of Denmark (DTU) by hosting an instance of CARP and ensuring compliance with GDPR and information security. The CARP framework supports in-app consent procedures, the triggering of EMA surveys and tasks, and the automatic collection of passive sensor data.

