#### 2.4.5 Subjective sleepiness and alertness

The KSS will be used to determine sleepiness levels at different times during the day. The KSS is a sleepiness rating scale from 1 (*very alert*) to 9 (*very sleepy, fighting sleep, and effort to keep awake*) We utilize the “state” dimension of the KSS in opposition to the “trait” dimension of the ESS. A 3-minute reaction-time test called the PVT test is used for alertness determination. The PVT test depicts the neurobehavioral effect of sleep loss or circadian misalignment, which is considered the gold standard. In this study, the KSS and the PVT test are EMAs, and the subjects will be prompted on their smartphone to fill these out four times a day during the 14 days before and 14 days after CPAP initiation. The specific prompting time will be at 08:00, 12:00, 16:00, and 20:00. In addition, the KSS and PVT EMAs will be available for the subject for an “at any time” registration. The subjects are instructed to take the test whenever they experience high subjective sleepiness episodes. Using this method, we bypass the global retrospective self-report necessary for filling out, for example, the ESS, which can be affected by recall bias.

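### Section 1.6 ties the EEG segments to the PVT prompt time, although the app records when each test was completed and self-initiated tests have no prompt

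*Protocol article*

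**What the plan says.** The second endpoint in section 1.6 relates EEG-derived biomarker candidates to established sleepiness measures. For the PVT it says how the EEG is to be located: "From the timestamps on PVT prompts to patients, we will identify segments of interest in the ULT-EEG recording". It then gives the purpose: "We will use this to validate the responses on the clinical scales given by patients".

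Section 2.4.5 describes the prompts. They run "four times a day during the 14 days before and 14 days after CPAP initiation", and the clock times are fixed: "The specific prompting time will be at 08:00, 12:00, 16:00, and 20:00". The test itself is short: "A 3-minute reaction-time test called the PVT test is used for alertness determination". Tests can also be taken without a prompt: "the KSS and PVT EMAs will be available for the subject for an “at any time” registration". The instruction for those is: "The subjects are instructed to take the test whenever they experience high subjective sleepiness episodes".

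Section 2.4.4 lists, among the advantages of the smartphone method, "providing digital timestamps with exact time registrations for when the subject completed their PVT test and KSS".

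**The concern.** A prompt time is when the phone asked. It is not when the patient was measured. The PVT and KSS are done in daily life, and a patient who is busy or asleep when the notification arrives will answer later. If the EEG is cut at the notification, the reaction time and the EEG describe different moments.

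Minutes matter here because the EEG markers are brief: section 2.9.3 defines a microsleep as lasting under 15 s, and section 2.9.4 describes vigilance staging in 1-s segments. Misaligned pairs would be expected to weaken the association that this endpoint looks for.

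The self-initiated tests are a separate problem that does not depend on delay. They have no prompt, so a rule based on prompts gives them no anchor. They are also the tests directed at the episodes where reduced vigilance is most likely to show in the EEG.

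**Working it through.** The plan gives no figure that depends on this rule, so there is nothing to reproduce. The check is a comparison of the sections, a count, and two illustrations.

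**Comparison of the sections**

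| Question | Section | Answer |
|---|---|---|
| What anchors the EEG segment? | 1.6 | The timestamp on the PVT prompt |
| When are prompts sent? | 2.4.5 | Four fixed clock times a day |
| When is the test done? | 2.4.5 | When the patient responds; no window stated |
| What time does the app record? | 2.4.4 | Completion of each PVT and KSS |
| What anchors a self-initiated test? | none | Not stated |

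**Prompts exposed to the rule**

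Inputs from section 2.4.5: 4 prompts a day, 14 days before and 14 days after CPAP initiation. Inputs from section 2.8: 12 patients calculated, 15 to be included.

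- Per patient: 4 × (14 + 14) = 112.
- 12 patients: 112 × 12 = 1,344.
- 15 patients: 112 × 15 = 1,680.

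These are ceilings on the number exposed, not counts of mismatched tests.

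**Overlap of segment and test**

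Assumption: a 3-minute segment that starts at the prompt. The article gives no segment length. For a delay of d minutes, the share of the test covered is max(0, 3 − d)/3.

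- d = 0: 3/3 = 100%
- d = 1: 2/3 = 67%
- d = 2: 1/3 = 33%
- d ≥ 3: 0%

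A longer segment, of L minutes from the prompt, contains the whole test when d + 3 ≤ L, but it then consists mostly of EEG from outside the test. At d = 15, L must be at least 18 and the test fills 3/18 = 17% of it. At d = 30, L must be at least 33 and the share is 3/33 = 9%.

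**Possible attenuation (illustration only)**

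Assumption: momentary vigilance has autocorrelation exp(−d/τ), so a correlation taken d minutes off is multiplied by that factor. Neither d nor τ is in the article.

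| τ (min) | d = 5 | d = 15 | d = 30 | d = 60 |
|---|---|---|---|---|
| 10 | 0.61 | 0.22 | 0.05 | 0.00 |
| 30 | 0.85 | 0.61 | 0.37 | 0.14 |
| 60 | 0.92 | 0.78 | 0.61 | 0.37 |
| 120 | 0.96 | 0.88 | 0.78 | 0.61 |

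At d = 0 the factor is 1. At a 15-minute delay it runs from 0.22 to 0.88, so the assumptions decide the answer.

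**With the completion time as anchor**

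If the test is completed at time T, the segment from T − 3 to T covers it fully whatever the delay. Self-initiated tests have a T as well, so each of them gets a segment.

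**The case against.** The best defence is that section 1.6 is loosely worded. A notification at a fixed hour hardly needs a timestamp to be found, and the timestamps that the article describes, in section 2.4.4, are completion times. The phrase in section 1.6 may therefore mean the timestamps of prompted tests. The same endpoint also correlates EEG with reaction time and KSS in general, without limiting this to prompted tests. Segment length, lead-in and accepted delay commonly belong in a fuller document, and section 2.7 says openly that the analysis plan is not fixed.

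Part of this stands. A reader might infer that completion times will be ignored and self-initiated tests left out. The article says neither; both are consequences of one sentence taken at its word. The missing segment length is not a fault in a journal article.

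It does not remove the point. Section 1.6 speaks of prompts to patients, and section 2.4.5 uses prompting for the notification, so the literal reading is also the natural one. No other anchor is given anywhere. What is criticised is a rule that the article states, not a detail that it leaves out. If the wording is only loose, the same one-sentence correction settles it.

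**Conclusion.** The point holds as a correction to the stated anchor, with minor to moderate severity. As written, section 1.6 points to a time that can precede the test by an unknown interval, and it provides no anchor for self-initiated tests, while the app holds the time that is needed.

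The direction of the effect, a weaker momentary relation of EEG to PVT and KSS, is what misalignment would be expected to produce. Its size cannot be determined from the article. A prompt answered at once causes no mismatch, and a segment long enough to span the test lessens it.

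Three stronger conclusions are not supported:

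- That all 1,680 prompted tests are mismatched. That number is the most that could be exposed.
- That the correlation shrinks by a particular factor. Every factor in the table rests on an assumed delay, an assumed τ and an assumed form of decay.
- That late answers cluster at the sleepiest moments, or differ before and on CPAP. This is plausible, but nothing in the article documents it.

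The sample size in section 2.8 rests on the ESS and is unaffected. Completion times are recorded under either reading, so the alignment can be put right at analysis.

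**What to change.** Make these changes in section 1.6:

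- Replace the prompt timestamp with the app-recorded completion time of each PVT and KSS.
- Define the EEG segment as the 3-minute test plus a fixed window before it, with the window length set before the data are examined.
- Apply the same rule to self-initiated tests and flag them, so that they can be analysed separately from scheduled ones.
- Use the prompt time only to describe response delay and non-response.

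The cost is a sentence or two in the endpoint section. The timestamps are already collected, so there is no added patient burden, no change in conduct and no change in sample size. Fixing the alignment in advance also removes one choice that could otherwise be made after seeing the results in a 15-patient study.
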